**Expected findings**

We expect that the clinical care of adults with suspected bacterial meningitis will be enhanced using the treatment delivered with EGDT, and the targets will be achievable. We expect this will translate to an improvement in mortality and reduce morbidity in survivors.

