**iv. i Intervention design**

EGDT will be delivered using a clinical care bundle, based on the ‘ABCD’ approach to resuscitation which has been developed and validated by the American and UK resuscitation councils (24) and consists of eight components, all of which are currently available in QECH and all of which are recognised existing clinical treatments which have supportive evidence of efficacy. The individual components of the bundle can be seen in table 1.

Staff training will form an important component of bundle delivery during phase 2a and ongoing through phase 2b, but will not form a specific bundle element. This is due to difficulties in assessing staff training when no formalised resuscitation training is available that is appropriate to resource limited settings.

The duration of the intervention will be 6 hours from initial screening to the point at which attempts to meet all targets have been achieved. Each subject will receive hourly observations including GCS scoring, blood pressure and pulse measurements. A lumbar puncture for the diagnosis of ABM will be performed at the earliest opportunity.

Study nurses and a clinical officer will deliver the bundle following training, using defined targets (table 2) within the AETC. At the end of the 6 hour study period, the bundle will stop, and the subject will be transferred to the medical ward for ongoing routine care. A flowchart of the study process is available in the appendix 9.

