***Secondary (to be measured at day 10 and day 40)***

1. Death
2. Persistent seizures requiring treatment
3. Significant neurological disability
4. Functional ability
5. Evidence of persistent renal injury
6. Blood and CSF bacterial load of *S. pneumoniae*

Death will be measured as a composite secondary endpoint (days to death/last known alive) using the following methods:

*Day 10 (acute)* – date of discharge (alive) or date of death will be recorded up to 10 days of inpatient antibiotic therapy.

*Day 40 (convalescent)* - Final outcome recorded ‘alive or dead’ following records from follow up or response to mobile telephone at until 6 weeks.

A history of seizures and functional ability since discharge will be taken, and endpoints 3-5 will be measured formally using the ***Modified Rankin score***, serum creatinine (to calculate eGFR), blood pressure and urine dip (for protein).

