**Follow up**

All participants who have been included based on CSF results will be followed up on the medical ward during their inpatient stay. Each participant will be reviewed daily and clinical progress data will be collected by the PI, the study clinical officer or one of the study nurses. The results of blood tests performed by the inpatient medical team will also be collected by download from the Spine recording system. For more detail on Spine please see data confidentiality on page 23.

All included subjects from Phases 1 and 2 surviving to discharge from hospital will be followed up weekly for 6 weeks (40 days) by text message sent to a nominated mobile phone (with consent from the participant). At six weeks each surviving participant will be invited to a study outpatient appointment at QECH. The outpatient follow up clinic will be staffed by the PI and the study clinical officer. Clinical data will be collected in outpatients to inform the secondary endpoints of the study.

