**Transport**

Study subjects will be asked to come back to outpatient follow up at 6 weeks from discharge. Expenses will be paid for this. Where a subject is unable to attend follow up for personal, geographical or financial reasons, attempts to collect data over the telephone will be made.

Staff leaving work at the end of the late shift will be driven home by taxi, funded from the study budget to enable secure and safe travel after hours.

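### The six-week Rankin data come from a clinic run by bundle staff who know the phase, so an apparent effect on disability could partly reflect rater expectation (minor)

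*Protocol*

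**What the plan says.** Under Endpoints (iv.ii), the secondary list includes significant neurological disability (3), functional ability (4) and persistent renal injury (5). The text then says that "endpoints 3-5 will be measured formally using the" modified Rankin score, together with serum creatinine, blood pressure and a urine dip. The last three serve the renal endpoint, so disability and functional ability rest on the Rankin score.

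Under Follow up (iv.vi), survivors are invited to an outpatient visit at six weeks. "The outpatient follow up clinic will be staffed by the PI and the study clinical officer", and "Clinical data will be collected in outpatients to inform the secondary endpoints of the study". For people who cannot attend, the Transport section says that "attempts to collect data over the telephone will be made". It does not name the caller.

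On roles, Intervention design (iv.i) says: "Study nurses and a clinical officer will deliver the bundle following training". Possible constraints and Personnel each provide for one clinical officer. The section on risk of serious adverse events has the PI train the team in every bundle element and review deteriorating participants.

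On knowledge of phase, Study design describes two consecutive phases, and the Timetable starts controls in January 2012 and the full bundle in January 2013. Data monitoring confirms that nothing is blinded or randomised. Expected findings records the team's view: "We expect this will translate to an improvement in mortality and reduce morbidity in survivors".

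The related safeguard is in Study design: data collection and follow-up are to be identical in both phases.

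**The concern.** The Rankin score is a graded judgement. When people who help run an intervention, expect it to work and know who received it also collect that grade, borderline cases can drift in the expected direction. Here the date tells the assessor the phase, so knowledge of phase and phase itself coincide for every participant. No later analysis can separate lenient grading from a bundle effect on this endpoint.

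What is at stake is the disability part of specific objective 3, which asks whether the bundle affects acute seizures and neurological disability in survivors. Seizure history is exposed to a lesser degree.

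**Working it through.** **Who assesses what**

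1. Endpoints 3 and 4 are measured by the Rankin score (Endpoints).
2. The six-week clinic that informs the secondary endpoints is staffed by the PI and the clinical officer (Follow up).
3. There is one clinical officer (Possible constraints, Personnel), and a clinical officer delivers the bundle with the nurses (Intervention design). The deliverer and the clinic assessor are therefore the same person.
4. The PI trains and supervises the bundle team (Risk of serious adverse events).
5. Inpatient progress data come from the PI, the clinical officer or a study nurse (Follow up). The nurses also deliver the bundle, so the day-10 assessment is no more independent.
6. The protocol describes no structured Rankin interview, scoring rule, second rater or masked re-scoring.

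**Illustration of scale**

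The plan gives no power calculation, significance level or disability rate for these endpoints, so there is no figure of its own to reproduce.

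Inputs from the protocol:
- 200-250 subjects, equally split (Sample size), so 100-125 per phase.
- 54% mortality (Background in the Executive summary), taken as equal in both phases.

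Survivors per phase = (N/2) × (1 − 0.54): 100 × 0.46 = 46 and 125 × 0.46 = 57.5, about 58, before any loss to follow-up.

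Assumptions that are not in the protocol:
- True disability p is 30%, 40% or 50% in both phases, so there is no real effect.
- A share m of disabled survivors (10%, 20% or 30%) is graded below the disability cut in Phase 2 only.
- The test is at a two-sided 5% level, which leaves 2.5% for a false benefit.

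The observed Phase 2 rate is p₂ = p(1 − m). The chance of a significant apparent benefit is Φ[(p − p₂ − 1.96·SE₀)/SE₁]. Here SE₀ = √(2·p̄(1 − p̄)/n) with p̄ = (p + p₂)/2, and SE₁ = √([p(1 − p) + p₂(1 − p₂)]/n).

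Worked case with n = 46, p = 0.30, m = 0.20:
- p₂ = 0.24 and p̄ = 0.27.
- SE₀ = 0.0926 and SE₁ = 0.0924.
- (0.06 − 1.96 × 0.0926)/0.0924 = −1.31, which gives 9.4%.

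| True disability | Survivors per phase | m = 10% | m = 20% | m = 30% |
| --- | --- | --- | --- | --- |
| 30% | 46 | 5.0% | 9.4% | 16.5% |
| 30% | 57.5 | 5.4% | 10.8% | 19.6% |
| 40% | 46 | 5.9% | 12.2% | 22.6% |
| 40% | 57.5 | 6.4% | 14.2% | 27.2% |
| 50% | 46 | 6.9% | 15.8% | 30.5% |
| 50% | 57.5 | 7.7% | 18.8% | 36.8% |

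The overall range is about 5-37%. Simulation of the same settings gave 4.9-7.9%, 9.2-19.0% and 16.2-37.4% for the three columns, and 2.2-2.6% with no misgrading.

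Few patients are involved. At m = 20%, 46 × 0.06 = 2.8 to 57.5 × 0.10 = 5.8 patients are regraded, and the apparent odds ratio is 0.74 (p = 30%) to 0.67 (p = 50%) with no true effect.

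**The case against.** **The assignment of the grade is inferred.** No sentence says who assigns the Rankin grade. The inference comes from reading Endpoints and Follow up together, and telephone data have no named collector. A reader might go further and infer that the PI and the clinical officer each design and deliver the bundle and then score its results. The protocol does not show that for either person. The officer's part in delivery is explicit, but nothing says that the officer designed the bundle. The PI's training and supervising role is explicit, but delivery is given to the nurses and a clinical officer. The concern needs only that phase-aware members of the intervention team collect the data, and that is stated.

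**There are safeguards.** Follow-up is identical in both phases, a named scale is used, and data are captured in coded form in REDCap. These deserve credit, but none of them prevents a person with a known expectation from resolving borderline cases differently by phase.

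**A structured form may exist elsewhere.** The Timetable completes and pilots data collection tools and SOPs before Phase 1, and a Rankin form could be among them. This is fair: its absence from the protocol does not prove that it is absent from the study. If it exists, the protocol need only cite it.

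**The numbers are assumed.** This stands in full. The disability rate, the misgrading rate and the test level are all imported, and the protocol defines no disability cut. Even at 20% misgrading, 81-91% of such trials would show no false significant benefit.

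**The consequences are limited.** This also stands. The primary endpoints are target achievement, and the next study depends on achievable targets. Guideline writing is tied to a mortality benefit. The protocol calls the study a pilot and warns that before/after designs can over-estimate benefit. It admits confounding by time and staff, though not by assessor expectation.

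**Conclusion.** The risk is real but minor. Two secondary endpoints use a judgement-based grade, and their six-week data come from a clinic run by bundle staff who know the phase and expect an improvement. An apparent effect on disability could therefore partly reflect rater expectation.

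The size is unknown. The 5-37% range shows what would follow from the assumed disability and misgrading rates. It is not an estimate of what happened in this trial. A reader might infer that any morbidity benefit would simply be the raters' expectation, and the documents do not support that. They show that the two explanations could not be told apart for these endpoints. They do not show that biased grading occurs. Death and creatinine, and the primary endpoints, lie outside the concern.

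**What to change.** In Endpoints, Follow up and Transport, specify one fixed set of questions on daily activities. Ask them in the same words in both phases, in clinic and by telephone, and record the answers in REDCap. Compute the Rankin grade from the answers by a rule set before Phase 1 follow-up starts, so that the interviewer does not choose it. The timing matters because control assessments cannot be repeated later. If such a form already exists among the SOPs, cite it.

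State in the report that disability and functional ability were assessed with knowledge of phase.

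The cost is one form, one scoring rule and a few minutes per survivor, with no added staff and no change in sample size. The fix reduces the bias but does not remove it, because phase-aware staff still ask the questions and record the answers. Masking the phase would need recorded or written assessments re-scored in mixed order by someone outside the team. That is a larger step than a secondary endpoint of a pilot requires.

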**iv.vii. Consent**

The aim of the bundle is speed of onset, and delays inherent in the informed consent process have the potential to impact on the success of the treatment. For most published studies testing sepsis bundle implementation using a before/after design, the need for informed consent was waived at institutional ethical review (27, 33-37). One study identified did not obtain informed consent from participants, and did not discuss any ethical concerns, or disclose institutional ethical review (38). However, we do not consider this approach appropriate for this setting.

We propose to use a two stage, delayed formal informed consent to enable the rapid onset of the bundle delivery. The consent process will be GCP compliant, and will consist of two steps: verbal assent by the participant or their guardian on admission and recruitment, and full informed consent when the subject is stabilised. This is planned for two main reasons. Firstly, the process of verbal assent to gain basic agreement for participation will facilitate rapid intervention. This followed by formal informed consent for ongoing participation at a later date is a standardised practice, recommended by the FDA and has been used in many trials of emergency interventions. Secondly, potential study participants are likely to be critically unwell on arrival at the hospital, and may have impaired consciousness, and therefore will not fulfil the requirements for standard GCP informed consent. This has been a problem for all studies that investigate critical illness testing rapid delivery of the intervention to a severely unwell participant.

**Verbal assent**

As the subject is identified as a potential study subject at triage in AETC, the recruiting study nurse will give verbal details of the study, and request verbal consent for inclusion ‘verbal assent’. If the answer is affirmative, the subject will be recruited and monitoring/bundle will be started immediately. An assent form will be signed at this point by the study nurse and if possible the patient or carer.

**Delayed formal informed consent**

Once the subject is stabilised, and able to talk (or a carer is present), formal written informed consent will be requested. If no carer is present and the patient is comatose, the subject will be included on the basis of best interests, until a time when a carer can be located to request consent.

No samples of tissue will be analysed, excepting those necessary for acute clinical management, until written informed consent has been given. If consent is denied at this stage then all records of that subject will be deleted from the main trial database. If the subject dies before either verbal assent or written informed consent can be given then data collected to that point will be used in the study and the carers will only be asked for written consent for the use of tissue samples in research laboratory studies

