**Requirements for GCP informed consent**

GCP formal informed consent can only be requested when the subject is physically and emotionally well enough to receive and comprehend the details given to the subject in the information sheet and by the study worker. Due to the high likelihood of comprehension being impaired during an acute episode of ABM, it is not appropriate to take informed consent at the acute admission point. Once the subject has been stabilised, and has improved to a point where s/he has reasonable comprehension and retention of information, formal written informed consent will be requested. However the bundle will need to be started before informed consent can be obtained.

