**Target and bundle sustainability related data**

Data will be collected on a weekly basis by the nurses through feedback to the PI to assess if the AETC staffing and equipment levels would be appropriate to deliver targeted care. An assessment will be made with the assistance of a local health economist of the additional cost of implementing each element of the bundle (if proven to be effective) into long term practice.

1. **Data analysis**

Each element of the bundle will be analysed separately to calculate the percentage of each clinical target was achieved.

Analysis will be primarily by intention to treat, and then per-protocol. Data will be collected using ‘redcap’ electronically and then transferred to SPSS/PASW statistical programme and GraphPad5™ software for analysis.

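### Deaths before written consent stay in the data while refusals are deleted, so retention depends partly on survival; the phase comparison suffers mainly if refusal differs by phase

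*Protocol*

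**What the plan says.** Consent has two stages. At triage a nurse asks for verbal assent: "If the answer is affirmative, the subject will be recruited and monitoring/bundle will be started immediately" (Verbal assent). Written consent comes later: "Once the subject is stabilised, and able to talk (or a carer is present), formal written informed consent will be requested" (Delayed formal informed consent). Requirements for GCP informed consent describes the same moment more narrowly, as the point "Once the subject has been stabilised, and has improved to a point where s/he has reasonable comprehension and retention of information", and accepts the consequence: "However the bundle will need to be started before informed consent can be obtained". For a comatose patient with nobody to speak for them, "If no carer is present and the patient is comatose, the subject will be included on the basis of best interests", until a carer is found.

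Two retention rules then stand side by side under Delayed formal informed consent:

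- Refusal: "If consent is denied at this stage then all records of that subject will be deleted from the main trial database".
- Earlier death: "If the subject dies before either verbal assent or written informed consent can be given then data collected to that point will be used". Carers are then asked only about research use of tissue samples.

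On the analysis, the Data analysis item states: "Analysis will be primarily by intention to treat, and then per-protocol". Comparing mortality between bundle recipients and controls is specific objective 2, and death is listed first among the secondary endpoints.

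**The concern.** Subjects are recruited and treated before written consent is sought, so refusal removes people after they have entered the study. Those who die before the request cannot be removed on this ground; those who live to be asked, or whose carer is asked while they live, can be. Whether a recruit stays in the analysed population therefore depends partly on the outcome being compared. An intention-to-treat analysis is meant to prevent exactly that.

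At stake are the mortality level in each phase and, if refusal differs between the observation phase and the bundle phase, the mortality comparison itself. Differing refusal is plausible, since patients and carers in the two phases see different care, but nothing in the Protocol shows that it will occur. Lower refusal in Phase 2 would look like a survival benefit, and higher refusal would hide one.

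**Working it through.** The Protocol states no refusal rate and no share of deaths before the consent request, so it has no figure on this point to reproduce. The size has to be worked out from the two rules under stated assumptions.

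Inputs from the Protocol:

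- Mortality M = 54% (Executive summary, Background).
- 125 per phase, from the upper end of 200-250 in total, split equally (Sample size).
- Cited absolute effect of 9-10 points (Early goal directed therapy to improve clinical management).

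Assumed:

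- e, the share of recruits who die before consent can be asked.
- r, the refusal rate among those asked.
- q, the later mortality of refusers.

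Observed mortality = [M − (1−e)·r·q] / [1 − (1−e)·r]

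**Direction.** This exceeds M only when q is below M. If refusers resemble the others who were asked, q = (M−e)/(1−e), which is below M whenever e > 0, so the push is upward. If carers refuse mainly for comatose patients who then die, q can exceed M and the push is downward.

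**All deaths before the request** (e = M, q = 0). There are 67.5 deaths and 57.5 survivors, so observed mortality = 67.5/(125 − 57.5r).

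| Refusal r | Observed mortality |
|---|---|
| 5% | 55.3% |
| 10% | 56.6% |
| 15% | 58.0% |
| 20% | 59.5% |

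With no true effect, 15% refusal in Phase 1 and 5% in Phase 2 gives 58.0% against 55.3%, a spurious reduction of 2.7 points.

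**Half the deaths after the request.** Of 125 recruits, 33.75 die first and 91.25 are asked, of whom 33.75 die later. Refusers are assumed typical of those asked, so observed mortality = (67.5 − 33.75r)/(125 − 91.25r).

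- r = 15%: 62.44/111.31 = 56.1%.
- r = 5%: 65.81/120.44 = 54.6%.
- Difference: 1.45 points before rounding.

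**Wider assumptions.** With e from 10% to 30% and the same 15% against 5%, the spurious difference is 0.6-1.6 points if refusers are typical. It is 4.4-5.9 points in the extreme case where every refuser survives. The sign reverses if the higher refusal falls in Phase 2.

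**Low refusal.** At r = 2% with e from 10% to 40%, mortality within a phase rises by 0.1-0.4 points (typical refusers) or 0.7-1.0 points (all refusers survive; the largest value is 0.99).

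**Equal refusal.** Take r = 10% in both phases, true mortality 54% against 45%, and all deaths before the request.

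- 54/(100 − 4.6) = 56.6%.
- 45/(100 − 5.5) = 47.6%.

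The difference stays at 9.0 points. The odds ratio is exactly unchanged, because survivors in both phases are multiplied by the same 0.9. With e = 20% and 15% instead, the observed difference is 9.1-9.5 points. Only a marked shift in timing disturbs this: with e falling from 30% to 10% at unchanged total mortality, 10% refusal in both phases gives −1.0 to +1.3 points.

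**Scale.** The standard error of the mortality difference is √(2 × 0.54 × 0.46/n), which is 6.3 points at 125 per phase and 7.1 at 100.

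**The case against.** The case on the other side is substantial.

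- The consent process is to be identical in both phases. Most of those asked will already have agreed verbally, and the treatments are standard care, so refusal of 15-20% has no support in the text. This stands as a limit on size. An identical procedure does not, however, guarantee identical refusal.
- A reader might infer that mortality must be overstated in both phases. The text does not support that. A carer can be asked while the patient is still comatose, so a deleted subject may later die.
- A reader might also infer that an effective bundle creates the bias by itself, because more people live to be asked. The equal-refusal calculation shows that it barely does.
- A third tempting reading is that the loss can never be measured. Deletion covers only the main trial database. Signed assent forms and a separate written record with study identifiers lie outside it, so refusals could probably be counted. Vital status at refusal is not assured there: the written record holds no clinical data and is destroyed at study end.
- Nor is every early death certain to count in the main comparison. The formal meningitis diagnosis needs CSF, and a patient who dies before lumbar puncture may not enter it.
- Death is secondary, and the study calls itself a pilot that cannot settle efficacy. Sensitivity tables may sit in an analysis plan that is not shown. This lowers the priority, but an analysis plan cannot use outcomes that the Protocol has ordered deleted.
- Deletion may be what the ethics committee requires. That bears on the remedy, not on whether the two rules are asymmetric.

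**Conclusion.** The point holds as an inconsistency worth a cheap repair. It does not show that the trial's mortality result will be wrong. The two retention rules make membership of the analysed population depend partly on surviving to be asked, contrary to the stated intention-to-treat principle.

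The usual effect is an upward push on mortality within a phase. A material distortion between phases needs mainly unequal refusal. On assumed refusal of 15% against 5% it is about 1.45 to 2.7 points, depending on how many deaths precede the request. The outer range is 0.6 to 5.9 points under the wider assumptions about refusers. These figures rest on 54% mortality in both phases and on refusal rates that the Protocol does not give. They compare with a cited effect of 9-10 points and a standard error of 6-7 points.

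**What to change.** Amend the Delayed formal informed consent section before recruitment starts.

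1. Subject to ethics committee approval, let each refusal leave one anonymous line in a log outside the clinical database: phase, recruited, and alive or dead when consent was refused. The clinical record is still deleted.
2. Report refusals by phase.
3. Beside the main mortality result, give the comparison with all refusers counted as alive, and with best-case and worst-case allocation of refusers between the phases.

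Letting people refuse samples, visits and vital status separately is optional and for the ethics committee to decide.

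The cost is a short amendment with committee approval and one extra table. The drawback is that a minimal anonymous count is kept for people who refused. The log has to be in place from the first recruit, because vital status at refusal may not be recoverable later.
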